### Study 3: Data Analysis and Dissemination

#### Data Analysis

Descriptive statistics will be generated from the sample using the demographic measures. Pearson's χ^2 ^test will be used to compare the proportions of categorical characteristics between the two intervention groups. The two-sample t-test will facilitate the comparison between the groups for characteristics measured on a continuous scale. This will allow us to evaluate the randomization, as we would expect to find roughly 5% of these findings to be statistically significant at the α = 0.05 level.

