##### Aim #1

To compare the 120-day post randomization mammography screening completion rates of individuals who receive a computerized mammography "implementation intentions" (**MI**^**2**^) intervention, versus a comparison computerized condition of general breast cancer prevention health education (**C**).

For this aim, both the outcome (120-day post randomization breast cancer screening completion) and predictor (treatment group) are dichotomous, so a 2 × 2 table will be generated to compare the proportions of those completing screening between the **MI**^**2 **^versus **C **intervention groups. A χ^2 ^statistic will be used to test the null hypothesis of no difference in these proportions between these two [67]. The distribution of measured and unmeasured confounding variables (beyond community location) should be relatively balanced between the intervention groups due to the random assignment of the intervention within communities and participants. However, if serious imbalances are apparent from the descriptive statistics described above, we will use unconditional logistic regression to model this dichotomous outcome. Predictor variables will include the intervention group and the unbalanced demographic characteristics to reduce the impact of such biases. Indicator variables identifying the community will also be included to control for this stratification variable as described by Agresti [67]. The results of this logistic regression will be transformed into estimates of the proportion screened [68] adjusted for the potential confounding variables. The fit of the model will be assessed using the Deviance statistic and the Hosmer-Lemeshow goodness-of-fit test [68].

To measure the impact of attrition on the part of the study participant, a sensitivity analysis will be performed. This can be done using the methods described by Rothman and Greenland [69] by examining what the results would be under various assumed scenarios for those missing the outcome. This will include a conservative imputation approach which will assume that all of those for whom this outcome is unknown were not screened during the 120-day post randomization period.

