##### Aim #3

To compare changes in mammography screening Precaution Adoption Process Model decisional stage from baseline to 120 days post randomization between individuals in the **MI**^**2 **^and **C **study arms.

The PAPM outcome is a six-level ordinal measure and the predictor (treatment group) is dichotomous, so a 2 × 6 table will be generated. The Cochran-Armitagestatistic will be used to test the null hypothesis of no difference in the distribution of scores between these two groups versus a trend [70]. If serious imbalances are apparent from the descriptive statistics described above, we will use the cumulative logit model [67]. Predictor variables will include the intervention group and the unbalanced demographic characteristics to reduce the impact of these biases. Indicator variables identifying the community will also be included to control for this stratification variable as described by Agresti [67]. The results of this regression will be transformed into estimates of the proportion moving from one stage to the next, adjusted for the potential confounding variables. The fit of the model will be assessed using the Deviance statistic.

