#### Sample Size and Sample Size Justification

This study will utilize Latina and AI/AN female participants from two distinct communities with approximately 121 randomized participants per community to test the main effects of the **MI**^**2 **^vs. **C **arms at 120 days post randomization. For this study, a total of 290 subjects will be randomized to either the **MI**^**2 **^or **C **treatment arms (to account for a possible 20% attrition rate from randomization to 120 day follow up). It is anticipated that 30% of those in the **MI**^**2 **^group will receive their breast cancer screening within the 120 day study period compared to 15% in the **C **group. A total of 242 subjects (121 per study arm) would have 80% power to detect the anticipated difference in screening rate between the **MI**^**2 **^and **C **groups at the α = 0.05 (two-sided) type I error rate (Table 5). Assuming up to a 20% attrition rate based on the research team's prior studies in rural Kansas, a total of 290 subjects will be randomized to either the **MI**^**2 **^or **C **treatment arms (145 per treatment). Additional screening rates were examined for study power (Table 5) to select an adequate sample size to detect clinically relevant differences. Numbers contained in Table 5 demonstrate that the sample will have at least 80% power to detect clinically relevant differences. Similar tables to Table 5 were also compared with varying sample sizes, with the final sample size selected being the choice that optimized both study power with the logistical constraints.

**Table 5 T5:** Power estimates (%) for a sample size of 121 subjects per group with α = 0.05 (two-sided)

		Breast Cancer Screening - Implementation Intentions	
		25%	30%
Breast Cancer Screening	10%	87	97
		
Controls	15%	Not Relevant	80

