#### Basis for intervention impact estimate

A study utilizing breast cancer survivors to serve as promotoras (similar to our community health worker paradigm proposed in this study) to promote breast cancer screening resulted in a 21% uptake in screening among 141 Latina women [71]. In a separate study with Native American women, a face-to-face patient navigator breast cancer education intervention resulted in a 11% uptake in screening mammography [72]. We expect a similar screening mammography uptake rates in our proposed study.

Screening uptake data from our current Healthy Living Kansas colorectal cancer implementation intentions intervention study are not yet available. However, other implementation intention-based studies have shown positive improvements in dietary fat intake [37], vitamin supplement intake [33], breast self-examination rates [34], vigorous physical activity rates [35], and functional ability after surgery [36]. Sheeran and Orbell [30] conducted a study to investigate the impact of an implementation intention intervention on cervical cancer screening rates - a behavior similar to the primary outcome of the proposed study, breast cancer screening. Sheeran and Orbell found the implementation intention intervention to increase cervical cancer screening attendance by 23% compared with a control group. Another recent study to assess the effect of implementation intentions on testicular self examination (TSE) in men found a 25% increase in self-reported TSE vs. a no intervention group. Both studies represent substantial behavioral changes resulting from implementation intentions-based interventions. Based on these studies, we would anticipate a similar increase in breast cancer screening in a general population. However, the participants who will be randomized into one of the proposed study arms represent traditionally underserved rural minority women whose access to mammography services may be hampered. Thus, we would expect for it to be more difficult to alter their breast cancer screening behavior. Nonetheless, based on the aforementioned assumptions, we anticipate a 25% increase in CRC screening rates for **MI**^**2 **^participants versus a 10% increase in breast cancer screening rates for **C **participants.

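### Aim 3's only named fit check, the deviance, cannot reject on individual records, and in Aim 1 it follows the screening rate rather than the fit

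*Protocol article*

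**What the plan says.** All references are to the protocol article, Study 3, Data Analysis.

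- **Aim #3.** The main analysis is a Cochran-Armitage test on a 2 × 6 table of Precaution Adoption Process Model (PAPM) stage by arm. Under serious imbalance a cumulative logit model is fitted instead, with arm, the unbalanced demographics and community indicators. Its results become adjusted proportions of women moving between stages. The only fit check is: "The fit of the model will be assessed using the Deviance statistic".
- **Aim #1.** The main analysis is a 2 × 2 chi-square test. The regression is conditional: "if serious imbalances are apparent from the descriptive statistics described above, we will use unconditional logistic regression to model this dichotomous outcome". On covariates: "Predictor variables will include the intervention group and the unbalanced demographic characteristics to reduce the impact of such biases", plus community indicators. On fit: "The fit of the model will be assessed using the Deviance statistic and the Hosmer-Lemeshow goodness-of-fit test".
- **Covariates.** The opening paragraph of Data Analysis provides for a "comparison between the groups for characteristics measured on a continuous scale", so some candidate covariates are continuous. Demographics lists age, education and income alongside categorical items.

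The article does not say whether the deviance is taken on individual or grouped data, what reference distribution it is compared with, or what follows from a poor fit.

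**The concern.** The residual deviance has a chi-square reference distribution when the data fall into a modest number of covariate patterns with many women in each. With one record per woman the saturated model reproduces each outcome exactly. For a yes/no outcome the deviance is then a function of the fitted probabilities alone. Its size reflects how common the outcome is, not whether the model is right. An ordinal outcome on individual records likewise has no valid chi-square reference.

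The consequence differs by aim. In Aim 3 no other check is named, and the cumulative logit model rests on proportional odds. If the arm effect differs across stage cut-points, the adjusted stage-movement proportions are distorted and the stated check would still report a good fit. In Aim 1 a second, usable check is named, so what remains is mainly the prospect of two tests disagreeing with no rule to settle it.

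**Working it through.** **Inputs.** 242 women analysed, 121 per arm, and two-sided α = 0.05 (Sample Size and Sample Size Justification). Planned rates from the same section: "It is anticipated that 30% of those in the" intervention group will "receive their breast cancer screening within the 120 day study period compared to 15% in the" control group. Basis for intervention impact estimate gives 25% v 10%. PAPM stage has six levels (Aim #3). Higher rates, covariate effects and forms of misspecification are assumptions of this review.

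**Step 1: the plan's own figure.** 121 per arm at 15% v 30% gives 80.2% power (pooled variance, no continuity correction). The plan states 80%, so inputs and plan agree.

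**Step 2: Aim 3, individual records.** The saturated log-likelihood is zero, so the deviance is −2 × the fitted log-likelihood. The fitted model contains the intercept-only model, whose deviance is −2N Σ pⱼ ln pⱼ. That is largest when the six stages are equally filled:

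- Maximum: 2 × 242 × ln 6 = 867.
- Parameters with arm, community and one covariate: 5 cut-points + 3 slopes = 8.
- Residual df: 5 × 242 − 8 = 1202; 5% critical value about 1284.

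Since 867 < 1284, the test cannot reject, whatever the data or the model (p > 0.9999 even at the maximum). The same holds if only five stages are occupied (maximum 2 × 242 × ln 5 = 779; df 4 × 242 − 7 = 961; critical value 1034) or four (maximum 671; df 720; critical value 784).

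**Step 3: does a working check exist for Aim 3?** Under an assumed violation of proportional odds, fitted stage proportions were off by up to about 8 percentage points. The ungrouped deviance flagged this 0% of the time. A likelihood-ratio test on the arm term flagged it 87% of the time.

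**Step 4: Aim 1, individual records.** Expected deviance = −2 Σ [p ln p + (1 − p) ln(1 − p)]. For the arm-only model df = 242 − 2 = 240, critical value 277.1.

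| Rates (C v MI²) | Arm-only deviance | p | Intercept-only deviance |
|---|---|---|---|
| 10% v 25% (planned) | 214.8 | 0.88 | 224.4 |
| 15% v 30% (planned) | 250.1 | 0.31 | 258.1 |
| 20% v 35% (assumed) | 277.8 | 0.047 | 284.7 |
| 30% v 45% (assumed) | 314.4 | 0.0009 | 320.2 |

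At the planned 15% v 30%, even a model with no covariates passes (258.1). The intercept-only deviance reaches the critical value only at an overall rate of about 26%.

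**Step 5: simulation for Aim 1** (n = 242, 5% tests; two sets of runs with different assumed covariate effects).

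- Correct model, deviance rejects: 0–3.5% at the planned rates, 43% at 20% v 35%, 79% at 25% v 40%, 98–99.8% at 30% v 45%.
- Badly wrong models (strong U-shape or crossover interaction omitted), deviance rejects: 0% at 10% v 25% and 2.3% at 15% v 30%.
- Hosmer-Lemeshow rejects a correct model 4–5% of the time at all rates. It catches the two strong errors 82% and 99.7% of the time at 15% v 30%. Under other assumed, milder errors it caught 33–42%, and in one case about 16%.

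**Step 6: would grouping rescue the deviance?** With 8 well-filled cells it rejects a correct model about 7% of the time and a wrong one 100%. Grouped by arm, community and age in whole years (40–74) there are about 116 patterns, roughly two women each. It then rejects a correct model 3%, 13%, 33% and 74% of the time at the four rate pairs in the table, so it still follows the rate.

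**The case against.** **Both regressions are fallbacks.** They apply only after serious imbalance, and no stated action depends on the fit result. A reader might infer that the trial's main comparisons are undermined. The documents do not support that: the chi-square test for Aim 1 and the Cochran-Armitage test for Aim 3 do not use these models. This stands, and it limits severity.

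**Aim 1 is not left to the deviance alone.** Hosmer-Lemeshow is named in the same sentence, holds its size and is usable on individual data. A reader might infer that a wrong Aim 1 model would go unnoticed. That does not follow, although detection ranged from about 16% to 99.7% with the assumed error.

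**The harm to Aim 1 estimates may be small.** With an omitted quadratic age term, in simulated trials that had a significant age imbalance, the bias in the adjusted arm difference was 0.4 percentage points or less (standard error 0.2). This stands for that form of error.

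**Rejection of a correct Aim 1 model is rare at the planned rates.** It needs rates above those in the plan. This stands.

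**Grouping is not stated.** If only coarse categorical covariates enter and the data are grouped, the deviance works, and the words could also mean a nested-model difference. This makes the point conditional. Step 6 shows that grouping does not help once age enters in whole years.

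**A proportional-odds test may sit in the full plan.** Its absence from an article is not a fault. The point here is different: the one Aim 3 check the article does state cannot do its job on individual records.

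**Conclusion.** The point holds, mainly for Aim 3 and secondarily for Aim 1, and is minor. It is conditional on serious imbalance triggering the models and on a near-continuous covariate making the data effectively one record per woman.

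Under those conditions the Aim 3 check is a guaranteed pass (at most 867 against about 1284). This is arithmetic and needs no assumption about effects. A reader might expect the deviance also to condemn sound Aim 3 models; on individual six-level records it can err only toward passing. The sizes of about 8 points of distortion and 87% detection rest on one assumed violation of proportional odds.

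For Aim 1 the deviance is uninformative at the planned rates and increasingly misleading at assumed rates of 20% v 35% and above. Hosmer-Lemeshow gives partial cover, but no rule says what to do when the two disagree.

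**What to change.** **Aim #3.** Replace the residual deviance with a test of proportional odds for the arm term: a score test, or a likelihood-ratio test against a partial proportional-odds model. If it fails, report the arm effect separately at each stage cut-point.

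**Aim #1.** Keep Hosmer-Lemeshow. Use the deviance only as a difference between nested models (for example arm by community, or a quadratic term for a continuous covariate) or on data grouped into well-filled cells.

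**Cost.** Two sentences and a few lines of code, with no new data and no change to the main tests. The downside is slightly more analysis and limited power of the added tests at n = 242, so a non-significant result should not be read as proof of fit.

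### The only named attrition scenario, all unknown scored as not screened, is called conservative without condition, but for the arm difference that is safe only when loss is similar in the two arms

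*Protocol article*

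**What the plan says.** Under Study 3, Data Analysis, Aim #1, the primary comparison is a chi-square test on the 2 × 2 table of arm by screening completion at 120 days. To gauge the effect of attrition, the article then plans a sensitivity analysis over several assumed scenarios for women with no outcome. It describes only one of them: "This will include a conservative imputation approach which will assume that all of those for whom this outcome is unknown were not screened" during the 120 days. The same rule applies to both arms, and no condition is attached to the label.

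The section Sample Size and Sample Size Justification randomizes 290 women ("145 per treatment") "to account for a possible 20% attrition rate from randomization to 120 day follow up". The allowance is one overall figure: "Assuming up to a 20% attrition rate based on the research team's prior studies in rural Kansas". The article neither splits it by arm nor says that loss is expected to be equal.

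**The concern.** Aim #1 is a comparison of two arms, so a reader will take the label to mean that the scenario works against finding a benefit of MI2. Setting every unknown outcome to not screened certainly lowers each arm's rate. Its effect on the difference between the rates depends on how many women each arm loses. If C loses more women than MI2, the rule can pull the C rate down further and move the comparison towards MI2.

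At stake is what the attrition check can be used to say. A result that is stronger after this imputation could be reported as having survived a conservative check when unequal drop-out had contributed to it.

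**Working it through.** **Inputs from the article.** Two-sided α = 0.05; 121 evaluable and 145 randomized per arm; anticipated screening of 30% (MI2) and 15% (C); attrition up to 20% overall; Pearson chi-square test.

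**Assumptions, not in the article.** The per-arm splits of the 20% loss. A common true rate of 15% to 22.5% under no effect (22.5% is the midpoint of 15% and 30%). Women with missing outcomes are screened at the same rate as completers in their arm.

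**The plan's own figure.** "A total of 242 subjects (121 per study arm) would have 80% power to detect the anticipated difference" is reproduced. With pooled variance and no continuity correction, n = [1.96·√(2·0.225·0.775) + 0.842·√(0.30·0.70 + 0.15·0.85)]² / 0.15² = 120.5, so 121 per arm, with power 80.2%.

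**Effect of the rule.** Let p be the true rate and d the proportion lost. Scoring the missing as not screened turns each arm's expected rate into p(1 − d), so

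imputed difference = pM(1 − dM) − pC(1 − dC) = (pM − pC) + (pC·dC − pM·dM).

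**No true effect (pM = pC = p).** The imputed difference is p(dC − dM), which is zero only if loss is equal. Rejection probabilities come from exact binomial enumeration of the chi-square test with 145 per arm:

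| Loss MI2 / C | True rate | Imputed rates | Spurious difference | Two-sided type I error |
|---|---|---|---|---|
| 20% / 20% | 15% | 12.0% v 12.0% | 0 | 5.0% |
| 20% / 20% | 22.5% | 18.0% v 18.0% | 0 | 5.1% |
| 15% / 25% | 15% | 12.75% v 11.25% | +1.5 points | 6.8% |
| 15% / 25% | 22.5% | 19.1% v 16.9% | +2.25 points | 8.0% |
| 10% / 30% | 15% | 13.5% v 10.5% | +3.0 points | 12.3% |
| 10% / 30% | 22.5% | 20.25% v 15.75% | +4.5 points | 17.0% |

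At 10% / 30% nearly all rejections favour MI2. Reversing the splits gives the same errors against MI2. The completers-only test stays at 4.8–5.0% in every row.

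**Planned effect (30% v 15%).** The shift is 0.15·dC − 0.30·dM, which is positive only if dC > 2·dM.

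- 20% / 20%: 24% v 12%, a difference of 12 points instead of 15. Power is 77%, against 79% in completers. The rule is mildly conservative here.
- 15% / 25%: 25.5% v 11.25%, or 14.25 points. The difference shrinks although MI2 lost fewer women. The power of the imputed test still rises, to 89% against 79% in completers: the relative difference has grown (ratio 2.27 instead of 2) and all 145 per arm are in the denominator.
- 10% / 30%: 27% v 10.5%, or 16.5 points, with power 96%.
- 30% / 10%: 21% v 13.5%, or 7.5 points, with power 40%.

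**Worked example at 10% / 30% loss.** 145 × 0.9 and 145 × 0.7 leave about 130 and 102 completers.

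- Completers: 35/130 (26.9%) v 20/102 (19.6%), z = 1.30, p = 0.19.
- All missing scored as not screened: 35/145 (24.1%) v 20/145 (13.8%), z = 2.25, p = 0.025.
- Missing MI2 women not screened, the 43 missing C women at the C completer rate (43 × 20/102 ≈ 8): 35/145 v 28/145, z = 1.00, p = 0.32.

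**The case against.** The strongest reply has four parts.

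- **It is one sensitivity scenario among several, in a condensed article.** This stands for the detail: a full list of scenarios can sit in the analysis plan, and its absence here is no fault. It does not rescue the label, which the article itself states.
- **At the one loss rate the article plans for, if shared equally, the rule is conservative.** This stands, as the 12-point result shows. The article does not attach that condition.
- **Unequal loss is conjecture.** Largely right. MI2 women leave with a personal printed contract and C women do not, but education by the community health worker, session length, gift card, follow-up call and contact requirements are common to both arms. Neither the size nor the direction of an imbalance can be predicted, and a threefold split such as 10% / 30% is an extreme illustration.
- **If the lost women really were unscreened, there is no bias.** Correct. With q the true rate among the lost, the distortion relative to full follow-up is qC·dC − qM·dM, which is zero when both q are zero. But q = 0 is exactly the untestable assumption being examined.

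Two stronger readings are tempting. A reader might infer that the rule always favours the arm with less loss and always widens the difference when C loses more. The first is exact under no true effect and on the ratio scale relative to completers, but not on the difference scale. The second fails at the planned rates unless C loss exceeds twice MI2 loss. A reader might also infer that the trial could declare success through this imputation. Nothing in the article lets it replace the chi-square test, and a completers' p of 0.19 beside an imputed p of 0.025 would show openly that attrition matters.

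**Conclusion.** The point holds in limited form. The article gives its one named attrition scenario a property that it has for each arm's rate, but for the arm contrast only when loss is similar by arm. With no true effect and lost women screened at the completers' rate, unequal loss alone creates an apparent effect of p(dC − dM) in favour of the arm with less loss. The inflation is modest at a 10-point imbalance (type I error about 7–8%) and material at a 20-point imbalance (about 12–17%). These are ranges under assumed splits and true rates, not forecasts. The primary test and the sample size are untouched. The label is worth correcting because this analysis exists to show how far attrition could have moved the result.

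**What to change.** In the attrition paragraph of Aim #1:

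1. Drop the word *conservative*, or qualify it as applying to each arm's rate, or to the contrast if loss is similar by arm.
2. Report loss to follow-up by arm beside the sensitivity results.
3. Name at least one scenario that is conservative for the difference. One example scores missing MI2 women as not screened and missing C women as screened at the observed C rate. At the planned rates with 20% loss in each arm, this gives 24% v 15%, a difference of 9 points.
4. Preferably, place these in a tipping-point table over arm-specific screening rates among the missing, keeping the all-not-screened case as one labelled cell.

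This should be settled before follow-up data are seen. The cost is a few lines of text and one table from data already being collected; the robustness statement may look slightly less favourable.

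A related passage should be reconciled at the same time. Table 2 lists having responded to the 120-day call as an inclusion criterion. If applied, that would remove the very women whom this analysis is meant to cover.
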